**1. BACKGROUND AND PURPOSE**

With the registrations of new generation of antiepileptic drugs (AEDs) during the past 20 years, there seems to be a tendency that new generation AEDs will replace traditional AEDs as the first-line choice for epilepsy. However, studies have shown discrepancies with respect to their effectiveness. Even in different guidelines, which AEDs should be recommended as the first-line choice has been unsettled.

This cohort study aimed to evaluate the effectiveness of two most frequently used AEDs, the traditional sustained-release formulation of valproate (SRVPA) and the new-generation drug topiramate, to find evidence supporting the rationality of this tendency or evidence querying it.

**2. STUDY OUTCOMES**

**2.1 Primary Outcome**

The primary outcome of this study is time to treatment failure

Treatment failure is defined as: in addition to other AEDs due to lack of efficacy; discontinuation of SRVPA or topiramate due to lack of efficacy, intolerable adverse events, lack of efficacy combined with intolerable adverse events, poor compliance, patients’ financial hardship, or a plan of pregnancy. A patient with poor compliance was defined as having discontinued SRVPA or topiramate treatment by his or her own volition.

**2.2 Secondary Outcomes**

Secondary clinical outcomes are the time to first seizure, the time from SRVAP or topiramate treatment to achieve 12-month remission of seizures, the time to 24-month remission of seizures. The incidence of clinically important adverse events and the incidence of intolerable adverse events directly leading to treatment failure were also analysed

Patients achieve 12-month (or 24-month) remission of seizures are defined as patients without any type of seizure for at least 12 months (or 24 months).

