**3.6 Statistical Analysis**

**3.6.1 Sample Size Calculation**

Sample size calculations were based on the primary outcome. It was assumed that the treatment failure for SRVPA and topiramate were 25% and 35% after one year, respectively. In this study, SRVPA was considered as an active comparator, there needed 415 patients for each group to achieve 90% power (β=0.1) at a 0.05 significance level to detect an equivalence hazard ratio of 1.35, assuming a dropout rate of 20% for both groups during the whole study.

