**3.6.3 Statistical Analysis Methods**

Kaplan-Meier estimates were used to describe the distribution of time to treatment failure, time to first seizure, time to 12-month remission, and time to 24-month remission. The log-rank tests were used to compare survival curves. The causes for censoring in Kaplan-Meier analysis were defined as follows: patients who were lost to follow-up, patients who died but whose death had no association with AED treatment and patients who were still receiving AED treatment at the end of this study. The censoring population was regarded as having no clinical outcome observed. Cox proportional hazard models (95% confidence interval) were used to analyse the relative risks expressed as hazard ratios (HR). In the final model, potential confounders (sex, age, type of epilepsy, seizure duration, number of previous AEDs and seizures at baseline) would be adjusted. Tolerability was assessed in the ITT population. To compare the reasons leading to treatment failure between SRVPA and topiramate, Chi-square tests and Fisher’s exact tests were used. The baseline characteristics of the two groups were compared using nonparametric tests, except the data represented as mean ± standard deviation (SD), which were analysed by using student’s t-test. All of the statistical analyses were performed with SPSS v. 13.0 software for Windows, using two-sided tests with a significance level of 0.05. No interim analysis is planned for this study.

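### Remission times tie at exactly 12 and 24 months by definition; with no tie method named, the adjusted hazard ratios for these two secondary outcomes may be pulled toward 1

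*Protocol*

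**What the plan says.** Protocol section 2.2 lists as a secondary outcome "the time from SRVAP or topiramate treatment to achieve 12-month remission of seizures", and time to 24-month remission beside it. It defines remission as "patients without any type of seizure for at least 12 months", with 24 months as the alternative.

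Section 3.6.3 plans Kaplan-Meier estimates for these outcomes and says "The log-rank tests were used to compare survival curves". Hazard ratios with 95% confidence intervals come from Cox models, and the final model adjusts for six potential confounders. On software it says "All of the statistical analyses were performed with SPSS v. 13.0 software for Windows". No method for tied event times is named.

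Section 3.1 describes an observational cohort in which clinician and patient choose the drug. The documents give no expected remission rate and no expected share of patients seizure-free from the first dose.

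**The concern.** The clock starts at first treatment and the event needs 12 (or 24) clean months, so nobody can have the event earlier. Everyone who never has a seizure after the first dose has it at exactly that point. Finer dating cannot break these ties, because the definition creates them.

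A Cox model treats time as continuous and needs an approximation when events tie. The Breslow approximation keeps all tied patients in the risk set for each tied event. That is harmless with few ties. When a large part of the risk set has the event at one time, the estimate moves from a hazard ratio toward a risk ratio, and the model variance no longer matches the estimator's spread.

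At stake are the adjusted hazard ratios for 12- and 24-month remission. In a cohort without randomisation, the adjusted estimate is the one a reader should rely on.

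**Working it through.** **Inputs from the protocol.** 415 per group and 20% dropout (3.6.1); two-sided 0.05 (3.6.3). The hazard ratio of 1.35 is borrowed from 3.6.1, where it belongs to the primary outcome, as a convenient true value. Section 3.5 sets reviews at week 2, months 1, 3 and 6, then half-yearly. Nineteen visits end at 6 + 14×6 = 90 months if Visit 1 is the start of medication, or 6 + 15×6 = 96 months if Visit 1 is week 2, so about 7.5 to 8 years. The plan has no remission figure of its own to reproduce.

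**Assumptions.** Breslow ties in the named software; the share in immediate remission; the later remission rate.

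**Step 1: limiting case, all events at one time.** With d1 and d0 events in the two groups, Breslow gives the risk ratio with model SE √(1/d1 + 1/d0). The sampling SD of the log risk ratio is √((1−p1)/d1 + (1−p0)/d0). The grouped-time hazard ratio is ln(1−p1)/ln(1−p0). Take 35% v 45% in remission, 415 per group, so d1 = 145.25 and d0 = 186.75:

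- Breslow estimate: 0.35/0.45 = 0.778
- Grouped-time hazard ratio: ln 0.65/ln 0.55 = 0.721
- Model SE: √(1/145.25 + 1/186.75) = 0.1106
- Sampling SD: √(0.65/145.25 + 0.55/186.75) = 0.0861; ratio 0.1106/0.0861 = 1.28

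This shows the mechanism at its extreme. It does not size the effect for this plan, where later remissions also count.

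**Step 2: a mass point plus later remissions.** Two-group simulation without covariates, 12-month outcome, 415 per group, 1,500 runs per setting, 20% dropout, 2 to 8 years of follow-up. Immediate remission in the reference group was 10, 20, 35, 50 or 65%, and later remission 0.3 per year. True hazard ratio 1.35:

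| Events tied at month 12 | Breslow HR | Efron HR | Breslow model SE / SD | Breslow 95% CI coverage | Power, Breslow | Power, log-rank |
|---|---|---|---|---|---|---|
| 16% | 1.345 | 1.349 | 0.99 | 0.958 | 0.94 | 0.94 |
| 31% | 1.334 | 1.349 | 1.04 | 0.957 | 0.95 | 0.96 |
| 49% | 1.307 | 1.347 | 1.08 | 0.944 | 0.93 | 0.96 |
| 65% | 1.261 | 1.337 | 1.20 | 0.886 | 0.89 | 0.96 |
| 78% | 1.206 | 1.319 | 1.55 | 0.747 | 0.80 | 0.97 |

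On the log scale Breslow keeps ln 1.334/ln 1.35 = 96% of the effect at 31% tied, then ln 1.307/ln 1.35 = 89%, ln 1.261/ln 1.35 = 77% and ln 1.206/ln 1.35 = 62%. With a slower later rate (0.15 per year) it gives 1.297 at 59% tied and 1.251 at 73%.

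With a true hazard ratio of 1, rejection rates were:

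| Tied | Breslow | Efron | Log-rank |
|---|---|---|---|
| 46% | 0.033 | 0.047 | 0.053 |
| 61% | 0.019 | 0.049 | 0.056 |
| 75% | 0.009 | 0.035 | 0.042 |

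Monte Carlo error near 0.05 is √(0.05×0.95/1500) = 0.006.

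**Step 3: how large might the tied share be?** This rests wholly on assumption. With the same kind of model and 2 to 8 years of follow-up, 30–50% seizure-free from the start gives 41–71% of 12-month and 45–75% of 24-month events tied. With only 10% seizure-free from the start and follow-up of 2 to 8 or 2.5 to 4.5 years, the shares are 15–28% and 17–37%. Models with patient-specific seizure rates and 20–55% seizure-free from the start have given anything from 28–71% to 60–81% at 12 months, and from 39–84% to 82–94% at 24 months. In each set the 24-month outcome is the more heavily tied.

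**The case against.** The strongest objection is that the documents name neither a tie method nor a tied share. That SPSS v13.0 uses Breslow is a statement about software, not something the protocol says; with Efron ties the problem largely disappears. Tie handling is also commonly left to a statistical analysis plan, which may exist. This stands in part, and it is why the point is conditional. But the protocol itself fixes the time origin, the model and one software version for every analysis. If the assumption about that version holds, an analysis plan could not choose Efron without departing from 3.6.3.

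A reader might infer that most remissions are tied. The documents do not support that as fact. Section 3.4 has doses raised slowly until control, and section 3.6.4 provides for patients with several previous drugs and frequent baseline seizures; both could lower the share. Section 3.6.4 equally provides for patients with no previous drug and no seizure in the baseline month, which could raise it.

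A reader might also infer that the error bars are simply too wide. They are not: the Breslow and Efron SEs agree (0.0769 v 0.0768 at 65% tied). The Breslow SE is too large only against that estimator's own shrunken spread, and under heavy ties the interval covers the true value too rarely because it is mis-centred.

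Finally, it is tempting to say that a real difference in seizure control would go unreported. The primary outcome already includes lack of efficacy, time to first seizure has no such mass point, and the log-rank test kept its size (0.042 to 0.057 over all null settings). That test is unadjusted, however, so in this cohort it cannot stand in for the adjusted hazard ratio.

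**Conclusion.** The point holds in conditional form. The tie at the earliest possible remission time follows from section 2.2 alone. If the software applies Breslow ties, the consequence for the Cox hazard ratios depends on the tied share: negligible below about 30%, material from about 50%, with a true 1.35 reported as about 1.31, 1.26 and 1.21 at 49%, 65% and 78% tied. The tests are then conservative, and the hazard ratio can disagree with the log-rank result on the same data.

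The conclusion rests on the Breslow assumption, on unstated remission rates and on simulations without covariates. It concerns two secondary hazard ratios and does not touch the primary outcome. It is a cheap improvement, not an error that undermines the study.

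**What to change.** Add one sentence to section 3.6.3: the 12- and 24-month remission outcomes are analysed with Efron or exact tie handling, or with a discrete-time complementary log-log model, using the same covariates, in software that supports the chosen method. With very heavy ties, exact or discrete-time handling is safer, since Efron itself fell to 1.319 at 78% tied.

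The cost is two models run outside SPSS v13.0 and a matching exception to the software sentence. Nothing is lost if few events turn out to be tied, because the methods then agree (1.345 v 1.349 at 16% tied).

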**3. METHODOLOGY**

**3.1 Study Design**

Observational cohort design is to assess the effectiveness of SRVPA and TPM in Chinese epileptic patients.

For the patients with a definite diagnosis of epilepsy, an appropriate AED was chosen by the clinicians, taking into consideration the efficacy and adverse events of the available AEDs, the clinical characteristics and the economic status of the patient. The patients also had the right to refuse the clinicians’ prescriptions and could discuss the drugs with the clinicians to decide which AED would be chosen.

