**3.5 Procedures**

The information recorded during the first visit included patient demographics, information about previous antiepileptic treatment, history of febrile seizures, birth traumas, epilepsy in first-degree family members, and neurological diseases (e.g., stroke, head injury, cortical development disorder, or intracerebral infection). A general physical examination and a neurological examination were performed. Laboratory examinations were carried out. Electrocardiogram (ECG) examinations were also performed, if necessary. Surface electroencephalography was performed on each patient to detect significant changes that might contribute to diagnosis. Computed tomography, magnetic resonance imaging and additional examinations, such as thyroid hormones, autoantibodies, and rheoencephalography, were carried out if clinically needed. Clinicians were asked to classify the types of epilepsy, epileptic syndromes, and types of seizures according to the criteria of the ILAE

The patients were asked to return for subsequent reviews at the second week, the first month, the third month, the sixth month and at successive half-year intervals from the date of initial medication. If clinical attention was necessary, more visits were scheduled between the regularly scheduled appointments. To control recall bias, each patient treated at our centres was asked to keep a medical diary with information on seizure onset, combinations with other drugs, adverse events, and hospital admissions. To control the loss of follow-up bias in the case of patients who did not appear for regular visits, follow-up data were obtained through telephone interviews or with structured questionnaire letters by mail. A patient who was lost of contact for more than one year was defined as a follow-up loss.

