**5 REMOVALS OF SUBJECTS FROM THE STUDY DRUG**

In accordance with the Declaration of Helsinki (48th General Assembly, Somerset West, Republic of South Africa, October 1996), subjects have the right to withdraw from the study at any time for any reason. Subjects may be removed from the study for the following reasons:

1. A serious or intolerable AE occurs

2. An intercurrent illness that, in the judgment of the investigator or sponsor, might invalidate the study or place the subject at risk.

3. At the request of the patients, whether economic or other reasons

If the reason for removal of a subject from the study is an AE, the AE and any related test results will be recorded on the record.

**When a subject is removed from the study:** the date of the last dose of study drug and all observations collected up to the time of termination will be recorded on the CRF along with the reason for termination

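### Economic status may influence both the choice of drug and the primary event but is not in the fixed adjustment set, leaving the primary hazard ratio open to confounding of unknown sign and size.

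*Protocol*

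**What the plan says.** - **Exposure.** Protocol section 3.1 sets up an observational cohort. Clinicians weigh efficacy, adverse events and "the clinical characteristics and the economic status of the patient", and patients may decline or discuss the choice.
- **Outcome.** Section 2.1 includes among the reasons for stopping that count as treatment failure "poor compliance, patients’ financial hardship, or a plan of pregnancy". Section 5 also foresees patients leaving "At the request of the patients, whether economic or other reasons".
- **Adjustment.** Section 3.6.3 fixes the final Cox model: "potential confounders (sex, age, type of epilepsy, seizure duration, number of previous AEDs and seizures at baseline) would be adjusted".
- **Baseline data.** Section 3.5 begins its list thus: "The information recorded during the first visit included patient demographics, information about previous antiepileptic treatment, history of febrile seizures". It goes on to further history and examinations. Income, insurance and economic status are not named there or in the section 3.3 schedule, which has only an unspecified demographics row.
- **Reasons for failure.** Section 3.6.3 states: "To compare the reasons leading to treatment failure between SRVPA and topiramate, Chi-square tests and Fisher’s exact tests were used". The section 3.3 schedule has a drop-out reason item at most visits, and section 5 has the reason for termination recorded.

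**The concern.** A factor that bears on which drug a patient receives, and separately on whether the patient reaches the endpoint, is a confounder. The protocol's own text puts economic status in both positions. If patients of limited means are found more often on one drug, that group will have more stops for cost even when the two drugs perform identically, and the adjusted hazard ratio will attribute the difference to the drug.

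The six listed covariates are demographic or clinical. They could remove the bias only so far as they happen to correlate with means. The per-protocol analysis in section 3.6.2 deals with loss to follow-up and does not touch this. What is at stake is the primary comparison: part of an apparent difference could be created, or a real one hidden.

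**Working it through.** **What the protocol gives.** Section 3.6.1 assumes 25% failure at one year on SRVPA and sizes on a hazard ratio of 1.35. It gives no distribution of economic status by drug, no price and no rate of cost stops, so there is no stated figure to reproduce. The 415 per group does not enter the calculation. Everything below is illustration under declared assumptions.

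**Assumptions.**
- The drugs are identical (true hazard ratio 1).
- Non-financial failure hazard: −ln(0.75) = 0.2877 per year. The plan's 25% is all-cause failure, so this label is an approximation (see below).
- Low-income patients stop for cost at an extra hazard h of 0.05 to 0.30 per year; other patients do not.
- Low-income shares on drugs A and B: 35% v 25%, 40% v 20% or 45% v 15%.
- Event counts: 225 and 500.

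**Spurious hazard ratio.** HR = (0.2877 + pA·h) / (0.2877 + pB·h). For example, with 45% v 15% and h = 0.30: (0.2877 + 0.135) / (0.2877 + 0.045) = 0.4227 / 0.3327 = 1.27.

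| Low-income share, A v B | h = 0.05 | h = 0.10 | h = 0.20 | h = 0.30 |
|---|---|---|---|---|
| 35% v 25% | 1.02 | 1.03 | 1.06 | 1.08 |
| 40% v 20% | 1.03 | 1.07 | 1.12 | 1.17 |
| 45% v 15% | 1.05 | 1.10 | 1.19 | 1.27 |

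Swapping A and B inverts each figure; 1.27 becomes 1/1.27 = 0.79.

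**Chance of two-sided p<0.05 with no drug effect.** z = ln(HR) / (2/√D) for D events, and the chance is Φ(z − 1.96) + Φ(−z − 1.96). For HR 1.27 (unrounded 1.271) and D = 500, z = 0.2394/0.0894 = 2.68, giving 76%.

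| Split | 225 events, h from 0.05 to 0.30 | 500 events, h from 0.05 to 0.30 |
|---|---|---|
| 35% v 25% | 5-9% | 5-14% |
| 40% v 20% | 6-22% | 7-43% |
| 45% v 15% | 7-43% | 9-76% |

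**Two approximations, pulling in opposite directions.**
1. The formula is the ratio at time zero. Low-income patients fail sooner and leave the risk set, so the average ratio is smaller. Allowing for this, the 76% falls to about 67%.
2. If the 25% already contains cost stops, the non-financial hazard is lower and the bias larger. With 15% low-income and h = 0.30, 0.75 = e^(−λ)(0.85 + 0.15·e^(−0.30)) = 0.9611·e^(−λ), so λ = 0.248. The ratio is then (0.248 + 0.135)/(0.248 + 0.045) = 1.31 instead of 1.27.

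**How demanding the top case is.** With an average low-income share of 30% and h = 0.30, cost stops contribute 0.09 of a total hazard of 0.2877 + 0.09 = 0.3777, or about 24% of all failures. Nothing in the protocol supports or excludes that.

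**Cross-check by another route.** Let low means multiply the failure hazard by 1.2 to 3, with 25% one-year failure on SRVPA and no drug effect. The apparent one-year hazard ratio is 1.04 to 1.27 for 20% v 40% low means (SRVPA v topiramate) and 1.06 to 1.38 for 30% v 60%. With 40% v 20% it is 0.96 to 0.78. The order of size is the same, and so is the dependence of the sign on an unknown.

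**The case against.** - **Economic status is only one consideration among several.** This stands. Section 3.1 also lists efficacy, adverse events and clinical characteristics, gives patients a say, and speaks of the available AEDs generally. A reader might infer that means drive the choice between these two drugs; the text supports only that they may influence it. If clinicians match drug to means, cost stops could even be reduced or balanced.
- **It may be recorded already.** Possible. The demographics are not itemised, so one cannot say the item is uncollected. Collection alone would not help, because the covariate list omits it.
- **Reasons for failure are examined.** True, so it would be wrong to say that no analysis separates hardship stops. The Chi-square and Fisher comparison would show an imbalance in counts. It neither adjusts the hazard ratio nor shows what the ratio would be without those stops.
- **Affordability is part of effectiveness.** A drug's own cost burden arguably is, given the aim of studying routine practice. A patient's means before treatment are not a property of the drug. This argues for adjusting for baseline means while keeping the composite.
- **This is a matter for the SAP.** The protocol itself fixes the covariates, and an SAP cannot adjust for a variable that was never collected.

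**Conclusion.** The point holds as a gap in confounder control that should be fixed. By the protocol's own account economic status can affect both drug choice and the primary event, and the stated model does not adjust for it. Over the full set of assumed values the spurious hazard ratio is 1.02 to 1.27, from negligible to a substantial part of the 1.35 used in sizing. False-positive rates are about 5-43% at 225 events and 5-76% at 500. The highest figures come from the widest split with the largest cost-stop hazard and use a time-zero ratio, so they belong at the upper end.

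A reader might infer that the result will be biased against one named drug, or by a known amount. The protocol gives no prices, income data or cost-stop rates, so neither conclusion is supported.

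**What to change.** 1. In section 3.5 and the Screen column of section 3.3, specify a baseline economic measure within the demographics (payer or insurance type and an income band), and add it to the adjusted confounders in section 3.6.3. This removes confounding by pre-existing means, as far as the measure captures them, and leaves each drug's own cost burden inside the effectiveness comparison. If the case report form already holds such an item, only the model needs changing.
2. Keep the composite primary analysis unchanged. Beside it, prespecify an adjusted cause-specific Cox sensitivity analysis that censors stops for financial hardship. Add a further run that also censors poor-compliance stops: section 2.1 defines these as the patient's own decision to stop, so cost-driven stops may be coded there. Both runs use reasons for stopping that are already recorded.

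The cost is one screening item, one model term (more parameters if the measure has several categories) and two extra Cox runs. The sensitivity analyses will have fewer events and wider intervals, and should be read as support for the main result, not as its replacement.
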